### Ethical considerations

The study protocol was approved by the Research Ethics Committee on 29 April 2010 and met all good clinical practice demands right. This study has been funded by the Spanish Ministry of Science and Innovation via the Instituto de Salud Carlos III (PI09/90304). The trial was registered with Current Controlled Trials, number ISRCTN83365316.

[http://www.controlled-trials.com/ISRCTN83365316]

## Discussion

The proposed implementation strategy should have impact at four levels: increasing the knowledge of clinical physicians and patients; changing attitudes; changing the habits and behaviour of professionals in their clinical practice, while taking into account the patient's preferences, as well as administrative and economic influences; and modifying results, which means improving the quality of care and, finally, the health of the population by following CPG recommendations [37,38]. In this study, we will focus on checking the degree of suitability of the guideline recommendations (in terms of treatment, referral to mental health services, and information to the patient) in the clinical practice. We will also check if health outcomes (anxiety and quality of life) are improving.

If the intervention proposed is effective, it could be generalized to other common problems present in primary care. The findings of the study can also inform a future updates of the guideline. The 'Guiasalud' project includes a methodological manual for GPCs implementation [39]; the study outcomes may serve, moreover, to evaluate this manual.

In addition, our project seeks to enhance the importance of multidisciplinary teams working in the design, implantation and evaluation of CPGs.

As for the limitations of this study, the design selected for this project is the best possible given the intervention, while seeking to avoid possible contamination. Although the number of clusters is enough for the randomization to balance the potentially confounding factors among themselves, the following must be taken into account:

1. Given the nature of the study, the intervention cannot be masked.

2. There may be a classification bias, given the difficulty professionals have for making specific diagnoses, but this should be minimized by the information contained in the guideline.

3. Patients will be enrolled in the study by their own professionals. This increases variability in the approach, which will be minimized, on the one hand, by the training of all participating professionals and, on the other hand, by the protocolization of the research and the implementation of the computer application of the data collection log in the computer programme. Moreover, the fact that the professionals themselves enrol patients will increase applicability in regular practice.

4. Although losses are contemplated in the follow-up, these are reduced in primary care because of the proximity of users to the system.

5. There may be a selection bias, because the selection and inclusion of patients will take place after randomisation of clusters. In order to be able to evaluate this bias, the information of those persons who decline to participate for each intervention group will be collected and compared.

In summary, the main contribution of our project is that it seeks to identify an effective strategy for implementing a CPG for the management of a common disorder present in primary care. Ensuring the appropriate uptake of guideline recommendations can reduce clinical variation and improve the care patients receive.

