### Masking

In the study, the patients, the professionals implementing the interventions, and those assessing the outcomes will not be blinded to the assignment group. However, analysis data will be performed by independent professionals blinded to the assignment group.

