### Intervention (see Table 1)

**Table 1 T1:** Interventions to professionals in both groups

Step 1	Centralized clinical session for the 16 PHCCs in which the GPC will be presented. Website 'Guiasalud'. Invitation to participate.	
Step 2	Primary Healthcare Centre RANDOMIZATION	

Step 3	Intervention group	Control group
	
	IMPLEMENTATION STRATEGIES: - Information and training about diagnosis and therapeutic plan - Election of opinion leader - Information and training structured to create anxiety disorder groups	Regular care

Step 4 (after visit 2)	IMPLEMENTATION STRATEGIES: - Audit and feedback - Reminders	Regular care

Step 5 (after visit 3)	IMPLEMENTATION STRATEGIES: - Audit and feedback - Reminders	Regular care

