#### Control group

1. The CPGs will be searchable on the intranet corporative system.

2. Centralized area clinical session with a duration of 60 minutes, to which each one of the professionals from each of the 16 health centres will be invited, and where the CPGs will be presented.

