#### Intervention group

The intervention, through the different strategies, has been designed to allow professionals to understand the guideline thoroughly, and also to implement its recommendations.

1. The CPG will be searchable on the intranet corporative system.

2. Centralized area clinical session with a duration of 60 minutes, to which each one of the professionals from each of the 16 PHCCs will be invited and where the CPG will be presented.

3. Information: Presentation of CPG in the PHCCs.

4. Training: two sessions with a duration of 60 minutes, imparted at PHCCs by the researchers.

5. Information and training to physicians, nurses, and social workers with the following contents:

a. Information and diagnosis: This would focus on the questions in the guideline that approach the definition of anxiety and its differentiation as a symptom and as a disorder. It would approach the semi-structured interview at the visit with an active methodology (roll-playing, *et al*.).

b. Pharmacological treatment and algorithms.

c. Non-pharmacological treatment: Group techniques (see table 2), bibliotherapy and medicinal herbs.

**Table 2 T2:** Group intervention in anxiety

First session	
	Presentation of the group General introduction to program Educational component:
	• What is the response to anxiety?
	• Why does it happen in daily life?
	• Is recovery possible?
	• What is the recovery process?
	The role of lifestyle in the response to anxiety (Part 1):
	• What do we do to take care of ourselves?
	• How lifestyle influences.
	• Introduction to relaxation and breathing.

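### Patients are identified after randomisation by unblinded professionals, with diagnostic training described for one arm only; the stated safeguards cover this bias path only in part

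*Protocol article*

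**What the plan says.** All references are to the Protocol article.

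- **Order of events.** Table 1 places randomisation of centres at Step 2. Discussion, limitation 5, accepts that "the selection and inclusion of patients will take place after randomisation of clusters".
- **Who recruits, and with what knowledge.** Limitation 3: "Patients will be enrolled in the study by their own professionals". Under Masking, neither patients nor the professionals delivering the interventions are blinded, and "those assessing the outcomes will not be blinded to the assignment group". Only the data analysts are.
- **What decides entry.** Under Subjects of the study, eligibility rests on a DSM-IV diagnosis of an anxiety disorder.
- **Intervention arm.** Table 1, Step 3, lists "Information and training about diagnosis and therapeutic plan" in the intervention column. Item 5a of the Intervention group section says this covers questions that "approach the definition of anxiety and its differentiation as a symptom and as a disorder", and the semi-structured interview taught by active methods.
- **Control arm.** Intranet access to the guideline, and a "Centralized area clinical session with a duration of 60 minutes, to which each one of the professionals from each of the 16 health centres will" receive an invitation. The intervention arm receives both of these too. Table 1 otherwise gives controls regular care.
- **Safeguards offered.** Limitation 3 refers to variability in approach, "which will be minimized, on the one hand, by the training of all participating professionals", and also to protocolisation and the computerised log. Limitation 5 adds that "the information of those persons who decline to participate for each intervention group will be collected and compared". Concealment of allocation adds consecutive sampling and a check of the inclusion and exclusion criteria. Statistical analysis adds a baseline comparison (item 2) and random-effects logistic regression for confounders (item 3).

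**The concern.** In a cluster trial that recruits after randomisation, central concealment protects the allocation of centres but not the selection of patients. Here the skill taught in one arm, separating symptom from disorder, is the skill that decides who enters the trial. The intervention arm could therefore enrol a different mix of patients from the control arm even if the implementation strategy had no effect on outcome. The primary endpoint is the proportion whose Goldberg anxiety score falls by two or more points from baseline, so a difference in case mix can look like a treatment effect or hide one.

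Two of the safeguards do not carry the weight placed on them. The training of all professionals has no counterpart in the description of the control arm. The decliner comparison starts one step too late, with patients who have already been recognised and invited.

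**Working it through.** **1. The training statement against the described arms**

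| Element | Intervention | Control |
|---|---|---|
| Guideline on intranet | yes | yes |
| 60-minute central presentation, by invitation | yes | yes |
| Two 60-minute training sessions at the centre | yes | not listed |
| Symptom versus disorder, semi-structured interview | yes | not listed |

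No training common to both arms is described. The nearest thing is the shared presentation, which is by invitation and is not described as teaching diagnosis. Table 1 puts the training after randomisation (Step 3) and before Step 4, which follows visit 2. That it precedes enrolment is an inference from this order, because the flowchart is not shown.

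**2. What each safeguard can see**

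The path into the trial is: attends, is recognised as a possible case, is diagnosed, is invited, then accepts or declines.

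- Decliner comparison: the last step only.
- Consecutive sampling: consecutive among patients whom the professional recognises.
- Eligibility check and common log: applied to patients already put forward. The log standardises recording and is not described as standardising case-finding.
- Baseline comparison and regression: can show or adjust for measured differences, such as baseline Goldberg score. Recorded diagnosis is weaker for this purpose, because it comes from the differently trained professionals.

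None of them counts patients lost before the invitation.

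**3. Illustration of what a shift would do**

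The plan's own sample size comes first, since the illustration uses it: DE = 1 + (20 − 1) × 0.01 = 1.19. Then 103 × 1.19 = 122.57, rounded up to 123 per arm, and 123 × 1.2 = 147.6, rounded up to 148 per arm, 296 in all. The stated figure reproduces.

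Inputs from the document: 148 per arm, 20% loss, ICC 0.01, 16 centres. Assumptions not in the document: 8 centres per arm, response near 50%, no true effect, a two-sided 5% test without covariates, and the sizes of shift.

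- Evaluable per arm: 148 × 0.8 = 118.4, or 118.4 / 8 = 14.8 per centre.
- DE at that size: 1 + (14.8 − 1) × 0.01 = 1.138.
- SE of the difference: √(2 × 0.25 / 118.4 × 1.138) = 0.0693.
- Rejection rate at shift b: Φ(b/SE − 1.96) + Φ(−b/SE − 1.96).

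| Shift b | b/SE | Rejection rate |
|---|---|---|
| 0 | 0 | 5% |
| 5 points | 0.72 | 0.1077 + 0.0037 = 11% |
| 6 points | 0.87 | 0.1369 + 0.0024 = 14% |
| 10 points | 1.44 | 0.3024 + 0.0003 = 30% |

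A 6-point shift would arise, for example, if the arms differed by 20 points in the share of patients who respond at 70% rather than 40%: 0.20 × (0.70 − 0.40) = 0.06. Using the plan's DE of 1.19 instead (118.4 / 1.19 = 99.5 effective per arm) also gives about 14% at 6 points.

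**The case against.** The strongest reply is that the protocol is open about the problem and does more than train staff and compare decliners. Limitation 5 names post-randomisation selection as a source of bias. There are also consecutive sampling, eligibility checks, a log that nothing suggests differs by arm, a baseline comparison and planned confounder adjustment. This stands in large part. A reader might infer that no planned check would reveal a case-mix shift. The document does not support that, because a shift in baseline Goldberg score could show in the baseline comparison. What remains is unmeasured differences and patients who never reach the log.

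A second reply is that limitation 3 may mean training in study procedures. That would suit a sentence about enrolment, and a condensed article might leave such training to the full protocol. The reading is possible, so one should not conclude that limitation 3 is simply false. As written, though, it has no support in the described control arm.

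Third, limitation 2 relies on the information in the guideline, which both arms can consult. A reader might infer that this safeguard makes misclassification differential. The documents support only that it may be, because the training on that content is listed for one arm.

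Finally, the sizes of shift are hypothetical and apply to an unadjusted test, although adjustment is planned. That is correct.

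**Conclusion.** The point holds as a weakness in design and in the stated safeguards, and it should be addressed. Unblinded professionals identify patients after centre randomisation, diagnostic training is described for one arm only, and limitation 3 must be reconciled with the Control group section and Table 1. The decliner comparison cannot detect patients who were not recognised or not approached. The other measures protect in part, mainly against measured differences.

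The direction of any bias cannot be determined, and the document gives nothing from which to estimate its size. The rates of 11%, 14% and 30% show what assumed shifts of 5, 6 and 10 points would do under the assumptions listed. A reader might take them as the trial's actual error rate, or as evidence that the arms will differ. They are neither. The conclusion also assumes that the Step 3 training precedes enrolment, as the order of Table 1 suggests.

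**What to change.** 1. **Common eligibility procedure.** Give all 16 centres the same instruction on eligibility in the Step 1 session, before randomisation, and make one DSM-IV inclusion checklist mandatory in the electronic log in both arms. Limit it to eligibility, with no treatment content.
2. **Recruitment counts.** Keep the decliner comparison and add counts by centre and arm of patients attended, identified, approached and enrolled. Take the denominator from all attendances in the health information system, which the protocol already uses for the number of patients visited. Coded anxiety consultations would not serve, because the coding depends on the same professionals.
3. **Main estimate.** Include the baseline Goldberg score, already collected, in the planned random-effects logistic model and treat that as the main estimate. This only names a covariate in a model already planned, and it does not remove unmeasured differences.
4. **Text.** Correct limitation 3 so that it says what training each arm receives and agrees with Table 1 and the Control group section.

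The cost is part of an existing session, a checklist in a log being built anyway, and one data extract. The downside is a slight dilution of the contrast, because control professionals also see the eligibility checklist. Restricting it to inclusion criteria is meant to keep this small, but the document gives no figure by which to judge it.
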